### Outcomes

All questionnaire based outcome measures will be performed at baseline, before surgery (after pre-surgery physiotherapy or waiting-list), as well as three months, one and two years after surgery. Two written reminders and if needed one telephone call will be used to enhance response rate. Subjective, physical assessment measures and TBC will be collected at baseline and after completion of the 9 weeks’ intervention.

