**Methods:**

This study is a single blinded, 2-arm, randomized controlled trial with follow-up after the completion of pre-surgery intervention as well as 3, 12 and 24 months post-surgery. The study will recruit men and women, 25 to 80 years of age, scheduled for surgery due to; disc herniation, spinal stenosis, spondylolisthesis or degenerative disc disease. A total of 202 patients will be randomly allocated to a pre-surgery physiotherapy intervention or a waiting list group for 9 weeks. The waiting-list group will receive standardized information about surgery, post-surgical rehabilitation and advice to stay active. The pre-surgery physiotherapy group will receive physiotherapy 2 times per week, consisting of a stratified classification treatment, based on assessment findings. One of the following treatments will be selected; a) Specific exercises and mobilization, b) Motor control exercises or c) Traction. The pre-surgery physiotherapy group will also be prescribed a tailor-made general supervised exercise program. The physiotherapist will use a behavioral approach aimed at reducing patient fear avoidance and increasing activity levels. They will also receive standardized information about surgery, post-surgical rehabilitation and advice to stay active. Primary outcome measure is Oswestry Disability Index. Secondary outcome measures are the visual analogue scale for back and leg pain, pain drawing, health related quality of life, Hospital anxiety and depression scale, Fear avoidance beliefs questionnaire, Self-efficacy scale and Work Ability Index.

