### Trail design

This study protocol describes a single blinded, 2-arm, randomized controlled trial with 2 year follow up and the 1 year follow up as primary end point. The protocol conforms to the SPIRIT 2013 recommendations.

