## Methods

### Study setting

A total of 202 consecutively selected patients will be included in the study. All patients are referred to the Spine Clinic at the University Hospital in Linkoping, Sweden. Individuals that fulfil the inclusion criteria will be asked to participate. After signed informed consent has been obtained, baseline measurement will be collected and randomisation will take place.

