1a. Specific movement and mobilisation - Mechanical loading strategies; repeated movements according to directional preference, mobilisation, and integration in a functional restoration program.	**X**	**TBC**
1b. Motor control exercise - Exercise focused on trunk and pelvic floor muscle activation and integration in a functional restoration program	**X**	**TBC**
1c. Traction - Manual Traction producing symptom reduction	X	**TBC**
2. Tailor-made general supervised exercise program - Individualised prescription (type of exercise and load) of aerobic, resistance, flexibility exercises with information documents and checklist for treatment, progression and dosage	X	**✓**
3. Behavioral approach: - Goal setting (establishment and regular reviews) - Strategies to minimize barriers to goal attainment, for example education regarding; ergonomics, postural alignment, patho-anatomical/physiological explanation - Self-mediated home exercise and physical activities (logbook)	X	**✓**
Advice regarding general physical activity recommendations	**✓**	**✓**
Education regarding surgery	**✓**	**✓**
Education regarding post-surgical rehabilitation	**✓**	**✓**
Pre-surgical re-evaluation	**✓**	**✓**

Spinal surgery and post-surgery rehabilitation in both groups is performed according to existing clinical routine [5]

✓ component mandatory, ***X*** component not allowed, ***TBC*** treatment based classification component with modifications

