### Statistical methods

Data collected at the longitudinal time points will be analysed according to the ‘intention to treat’ (ITT) principle. Data analysis according to ITT requires that data for every patient, regardless of level of intervention compliance, data missing at follow-up or due to drop-out, will be included in the group to which they are randomised [50]. To perform an ITT analysis, missing data will be replaced through multiple imputation methods. In an attempt to determine the sensitivity of the ITT data, it will be compared to per-protocol data from patients who have complied with the original study protocol. Alternative analyses will also be performed to take treatment compliance into consideration. Analysis of variance ANOVA will be used to investigate within and between group differences in longitudinal outcome measures. Within and between group Cohens *d* effect sizes will also be calculated. Multivariate regression will be used to analyse potential predictors of long term outcomes.

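### The primary 1-year ODI is timed from surgery, so randomised patients who are never operated on have no assessment date and would be imputed from operated patients

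*Protocol article*

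**What the plan says.** The Trail design section describes a "randomized controlled trial with 2 year follow up and the 1 year follow up as primary end point". The Outcomes section schedules every questionnaire, the ODI included, at baseline, before surgery, "as well as three months, one and two years after surgery". The Abstract (Methods) uses the same anchor: "follow-up after the completion of pre-surgery intervention as well as 3, 12 and 24 months post-surgery".

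Randomisation comes well before that anchor. Under Study setting, "After signed informed consent has been obtained, baseline measurement will be collected and randomisation will take place". The Abstract adds that patients are "randomly allocated to a pre-surgery physiotherapy intervention or a waiting list group for 9 weeks". The order is therefore baseline, randomisation, nine weeks of physiotherapy or waiting, surgery, and then the clock for the primary endpoint.

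The Statistical methods section keeps every patient in the randomised group, whatever the compliance or drop-out, and states: "To perform an ITT analysis, missing data will be replaced through multiple imputation methods". A per-protocol comparison serves as the sensitivity analysis. No section says when a patient who is not operated on is assessed, or how that patient enters the 1-year analysis. The only related provision is the general 35 % allowance for loss to follow-up under Sample size.

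**The concern.** The clock for the primary endpoint starts at an event that follows randomisation and that the intervention could affect. The aim is to improve function and pain before the operation, in patients whose pain level is part of the reason for operating. Some may decline or postpone surgery, and the two arms need not do so equally. This has two distinct consequences.

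- **Never operated.** The patient has no date one year after surgery, so the schedule requests no 1-year ODI, although a questionnaire could have been sent.
- **Deferred.** The patient is assessed one year after surgery, but at a longer interval from randomisation. If delays differ by arm, the arms are compared at different times since randomisation.

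The first consequence matters more. If all 1-year data come from operated patients, the imputation model can only predict what a non-operated patient would have scored had surgery taken place. That is not the outcome of the patient as randomised. The visit schedule decides what is collected, so a later analysis plan cannot recover an ODI that was never requested.

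**Working it through.** **1. The plan's own figure.** Inputs from Sample size: difference 10, SD 20, power 80 %, significance level 0.05 (taken as two-sided). The normal approximation gives n = 2 × (1.960 + 0.842)² × 20² / 10² = 62.8, so 63 per arm. The two-sample t-test gives 63.77, so 64, as stated. With 202 randomised and 35 % lost, 202 × 0.65 = 131.3 remain (65.65 per arm), with t-test power 0.811. The sample size reproduces and is not in question.

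**2. What the schedule yields for each kind of patient.**

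| Patient | 1-year ODI under the written schedule |
|---|---|
| Operated on after the 9 weeks | Observed, at least 9 + 52 = 61 weeks after randomisation |
| Operated on after a further delay of d weeks | Observed, about 61 + d weeks after randomisation |
| Never operated on | No date defined; under the general rule, imputed |

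**3. Bias from imputing non-operated patients.** In an arm with a share p of non-operated patients and a mean gap g between their imputed and true ODI, the arm mean is wrong by p × g. The between-arm difference is wrong by p₁g₁ − p₂g₂. If the gap is the same in both arms, this becomes (p₁ − p₂) × g. The article gives neither p nor g, so both columns of inputs below are assumptions.

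| Excess non-operated in one arm | Gap in ODI points | Bias in the difference | Share of the 10-point target |
|---|---|---|---|
| 5 % | 5 | 0.05 × 5 = 0.25 | 2.5 % |
| 10 % | 10 | 0.10 × 10 = 1.0 | 10 % |
| 20 % | 15 | 0.20 × 15 = 3.0 | 30 % |

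Against the planning SD of 20, the middle row is 1.0 / 20 = 0.05 SD and the last is 3.0 / 20 = 0.15 SD. The sign of g is unknown, so the direction is too.

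**4. Power is a side issue.** Suppose non-operated patients in the physiotherapy arm are lost on top of the 35 %. With 5 % not operated on, 101 × 0.95 × 0.65 = 62.4 remain in that arm against 65.65 in the other, and power is 0.801. With 20 %, 101 × 0.80 × 0.65 = 52.5 remain and power is 0.764. If these patients fall within the 35 %, power stays above 80 %. The allowance can absorb lost precision, but it does nothing about bias from losses related to treatment.

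**The case against.** The strongest reply is that this is an unstated operational detail. The article never says that non-operated patients receive no questionnaire. It promises to include everyone as randomised, it describes reminders and a telephone call, and its time-schedule figure cannot be seen here. A mailing rule could well sit in the full protocol. This part stands to the extent that imputation of these patients is inferred from the general missing-data rule, not stated. It does not remove the point, because surgery as time origin is a stated rule, given in both the Abstract and the Outcomes section, and that rule leaves a never-operated patient without a 1-year date.

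Second, the ODI is also collected after the 9-week period in both arms and could inform the imputation. That may narrow the gap. The link from that score to the 1-year score would still be learned from operated patients only.

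Third, the evidence for differential cancellation is thin. A reader might infer from Table 1's "Pre-surgical re-evaluation" that the decision to operate is reopened. The item is mandatory in both arms, may simply be the repeat assessment described under Data collection methods, and is not said to reopen anything. A reader might also take the Background's favourable remarks on non-surgical care as a forecast of cancellations. Those remarks concern care before the decision about surgery, whereas the trial enrols patients already scheduled. Influence on surgery is therefore possible, but the document does not show it.

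Fourth, timing a surgical-pathway trial from surgery is defensible. Moving every patient to a randomisation clock would change the question and could catch a long-deferred patient soon after the operation. This is accepted, and the fix below keeps the surgery clock for operated patients.

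**Conclusion.** The point holds at moderate severity. The primary endpoint is tied to an event after randomisation. Followed as written, the plan would replace an obtainable 1-year ODI in never-operated patients with a value imputed from operated ones. Deferral leads to unequal time since randomisation.

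Two stronger readings are not supported. A reader might infer that imputing these patients breaks the intention-to-treat promise. The Statistical methods section names multiple imputation as its means of carrying out that analysis, so there is no contradiction. A reader might also infer that deferred patients lose their 1-year value. Deferral only moves the visit later.

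Size and direction are unknown because no cancellation rate is given. The range of 0.25 to 3.0 ODI points is an illustration. It assumes a 5 to 20 percentage-point excess of non-operated patients in one arm, a 5 to 15 point gap that is equal in both arms, and imputation of all such patients. The upper end needs both assumed maxima at once.

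**What to change.** - Keep the visits timed from surgery for operated patients.
- For randomised patients not operated on, count the 3-, 12- and 24-month questionnaires from the originally scheduled surgery date, or from the end of the 9-week period if no such date was recorded. State the choice in advance and apply it identically in both arms.
- Analyse the ODI these patients return in the group to which they were randomised. Impute only questionnaires that are not returned.
- Report by arm the proportion operated and the time from randomisation to surgery, and add a sensitivity analysis by time since randomisation.

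The cost is a mailing rule, a few sentences of protocol text and a few more questionnaires. No extra patients or clinic visits are needed, and clinical care does not change. The downside is that the 1-year time point then mixes time since actual surgery with time since planned surgery, which the sensitivity analysis is meant to examine. The trial is ongoing, so the rule should be set before more of these assessments fall due without being requested.

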#### Primary outcome measure

The primary outcome measure will be patient self-reported function and activity limitation measured by Oswestry Disability Index (ODI) [34]. ODI contains ten items investigating pain related function impairment and activity limitations with six answer alternatives for each item. The sum score is between 0-100 %, with higher values representing higher functional disability score [34].

#### Secondary outcome measures

Pain will be evaluated with VAS [35], pain drawing and pain duration [36]. Health related quality of life will be evaluated with SF-36 [37] and EQ-5D [38]. Anxiety and depression will be evaluated with the Hospital Anxiety and Depression Scale (HADS) [39] and self-efficacy with Self-efficacy scale (SES) [40]. Fear avoidance will be measured by Fear avoidance belief questionnaire (FABQ) [41]. Work will be assessed by general information of work and Work Ability Index (WAI) [42]. Patient reported treatment effects will be measured by Patient reported global treatment effects and patient enablement instrument (PEI) [43]. Expectations, sick-leave, lifestyle behavior, previous healthcare consumption and adverse events will also be measured. Patients randomized to pre-surgical physiotherapy will be evaluated with the Patient Specific Functional Scale (PSFS) [44] three times during the intervention. Subjective, physical assessment measures and TBC will be used as secondary outcome measures.

### Participant timeline

The study design is outlined in Fig. 1.

**Fig. 1 Fig1:**
[figure not shown]
Time schedule of enrolment, interventions and assessment

### Sample size

Based on a minimally clinical important change of 10 % on the ODI [45], a standard deviation for the ODI =20, a significance level of *p* = 0.05, a power of 80 %, an estimated 64 patients are required in each of the intervention groups, at the primary endpoint. The current sample size of 202 patients allows for a 35 % loss to follow-up while maintaining >80 % statistical power.

### Allocation

Block randomization will be used with smaller block size at the end of the study. Initially two blocks of 60 will be created and then subsequent blocks of 20, 8 and 4. For each randomization block, sealed opaque envelopes will be prepared with a 1:1 ratio of allocation to the pre-surgery waiting list group as well as the pre-surgery physiotherapy group. After baseline measurement, an independent physiotherapist working at the Spine Clinic will open a sealed opaque randomization envelope and inform the patient about group allocation. The same physiotherapist will contact the physiotherapy center where the patient will receive treatment.

### Blinding

The physiotherapist performing the clinical measures and assigning a treatment based classification will be blinded to the randomization, while patients and the physiotherapists treating the patients cannot be blinded.

### Data collection methods

#### Clinical tests and TBC procedure

Baseline subjective and physical assessment measures will be assessed by a physiotherapist. The same assessment will be conducted at follow up after the intervention. The subjective assessment will include information on symptom duration, prior LBP, distribution of symptoms, symptom aggravating and easing positions (sitting, standing or walking), time tolerated in positions (sit, stand and walk) as well as signs of centrally disturbed pain modulation. Physical assessment will include test for aberrant movements, neurological tests (myotomes, dermatomes and reflexes) for spinal segmental levels L4-S1, straight leg raising, range of motion for internal rotation of hips, posterior-anterior-test lumbar segmental provocation test (PA-test), Sacroiliac joint provocation tests (SI-tests), test for symptom centralization, prone instability test, active straight leg raise (A-SLR), Trendelenburg test, isometric bilateral quadriceps strength and 10 m walking-test [46, 47].

The following TBC will be utilized; a) Specific exercises and mobilization, b) Motor control exercises or c) Traction. The TBC criteria for patient’s subjective and physical examination findings which has been outlined in previous publications [26–28] will be utilized except for the “Specific exercises” and “Manipulation” classifications in the original TBC being collapsed to one classification named “Specific exercises and mobilization”. This means that manipulation will not be used as a treatment classification. The reason for this is that the patients included in the study have long-lasting pain that does not fulfil the TBC criteria of symptom duration < 16 days for the manipulation classification [27]. Furthermore, literature suggests that 25 % of the patients fulfill criteria for more than one classification and for 68 % of these cases it is the combination of criteria for “Specific exercises” and “Manipulation” [26]. In the “Specific exercise and mobilization” classification, a test for centralization with lumbar spine flexion combined with rotation in side lying position will be added, to assess more directions than only sagittal plane movement. This position is commonly used in clinical practice for assessment and treatment of patients with sciatica. If repeated exercises only give an unstable centralisation, where the pain is reduced or abolished during the repeated movement testing or positioning but after resuming a weight bearing position for one minute, the pain intensity level returned to the pre-testing intensity, patients will be classified to this classification [48]. This added criteria is useful in patients who have significant activity limitation due to pain, are too deconditioned to perform repetitions of tests or are patients who activity limiting symptoms are not painful such as in some spinal stenosis cases. In the PA-test, segmental pain will be documented, but not hypo- or hypermobility, due to lack of reliability in segmental motion restriction [49]. The tests “Active straight leg raising” (ASLR) and Trendelenburg will be added as criteria for the “Motor control exercises” classification [28]. The TBC is outlined in Fig. 2.

**Fig. 2 Fig2:**
[figure not shown]
Treatment based classification (TBC) [26–28] used in the trial

### Data management

Data will be stored at the research department at Linköping University, not allowing for identification for individuals.

### Statistical methods

Data collected at the longitudinal time points will be analysed according to the ‘intention to treat’ (ITT) principle. Data analysis according to ITT requires that data for every patient, regardless of level of intervention compliance, data missing at follow-up or due to drop-out, will be included in the group to which they are randomised [50]. To perform an ITT analysis, missing data will be replaced through multiple imputation methods. In an attempt to determine the sensitivity of the ITT data, it will be compared to per-protocol data from patients who have complied with the original study protocol. Alternative analyses will also be performed to take treatment compliance into consideration. Analysis of variance ANOVA will be used to investigate within and between group differences in longitudinal outcome measures. Within and between group Cohens *d* effect sizes will also be calculated. Multivariate regression will be used to analyse potential predictors of long term outcomes.

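### The named ANOVA carries no baseline covariate although ODI is measured before randomisation; adjusting 1-year ODI for baseline would gain precision at no cost in data

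*Protocol article*

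**What the plan says.** All places are in the protocol article.

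- **Method.** Statistical methods: "Analysis of variance ANOVA will be used to investigate within and between group differences in longitudinal outcome measures". No covariate, group-by-time term or primary contrast is named. Regression appears in that section only for the search for predictors of long-term outcome.
- **Baseline data.** Outcomes: "All questionnaire based outcome measures will be performed at baseline, before surgery", and again at three months, one year and two years after surgery. Study setting and Allocation place the baseline measurement before the randomisation envelope is opened.
- **Primary time point.** The trial design section sets it at one year.
- **Sample size.** "Based on a minimally clinical important change of 10 % on the ODI", "a standard deviation for the ODI =20", "a significance level of *p* = 0.05" and 80 % power lead to "an estimated 64 patients are required in each of the intervention groups, at the primary endpoint". The section adds: "The current sample size of 202 patients allows for a 35 % loss to follow-up while maintaining >80 % statistical power".
- **Diagnosis.** Eligibility criteria list four diagnoses. Allocation describes 1:1 blocks and names no stratification factor.

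**The concern.** A pre-randomisation measurement of the primary outcome is usually the strongest single predictor of its later value. Neither common form of ANOVA makes the best use of it. A comparison of 1-year scores ignores it. A repeated-measures ANOVA with baseline as one level of time reduces, for baseline and 1 year, to a comparison of change scores. That subtracts the whole baseline value, and so adds noise when the correlation is modest. Analysis of covariance (ANCOVA) estimates how much of the baseline to subtract. In large samples it is at least as precise as either alternative, and it also removes the effect of chance baseline imbalance.

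At stake is precision in a trial that budgets for 35 % loss and would then have only just over 80 % power. The data needed for the better analysis are already part of the design.

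**Working it through.** **Inputs from the protocol article.** Difference 10 ODI points; SD 20; significance level 0.05; power 80 %; 202 randomised (101 per arm); 35 % loss tolerated. Sidedness is not stated; two-sided reproduces the figure (one-sided would need 50 per group).

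**Input not in the documents.** The correlation r between baseline and 1-year ODI. It is an assumption and is shown over a range.

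**1. The plan's own figure.** Standardised difference d = 10/20 = 0.5. A two-sided t-test at 80 % power needs 63.8, so 64 per group; at 64 the power is 0.801. For 35 % loss, 128/0.65 = 197, and 202 covers this. After 35 % loss, 202 × 0.65 = 131.3 remain, or 65.65 per arm, with power 0.811. The stated figures are correct for an unadjusted two-group comparison at 1 year.

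**2. Variance of the three analyses, relative to the 1-year score.**

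- 1-year score alone: 1.
- Change score, equal SDs at both times: 2(1 − r).
- ANCOVA on baseline, large samples: 1 − r².

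ANCOVA is never the largest. It is at most 1, and 2(1 − r) − (1 − r²) = (1 − r)² ≥ 0. Equal SDs are not needed for this ordering. With baseline SD s₀ and follow-up SD s₁, the change-score variance exceeds the ANCOVA variance by (s₀ − r·s₁)² ≥ 0. So the direction of the gain does not depend on r; only its size does.

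**3. Power at 65.65 per arm** (noncentral t; d = 0.5/√[2(1 − r)] for change, d = 0.5/√(1 − r²) for ANCOVA).

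| Assumed r | 1-year score | Change score (equal SDs) | ANCOVA |
|---|---|---|---|
| 0.3 | 81 % | 67 % | 85 % |
| 0.4 | 81 % | 74 % | 87 % |
| 0.5 | 81 % | 81 % | 91 % |
| 0.6 | 81 % | 89 % | 94 % |

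In patient numbers, ANCOVA needs about 128 × (1 − r²) evaluable patients for the planned power: 116 at r = 0.3, 108 at r = 0.4 and 96 at r = 0.5.

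**4. How fragile the change-score shortfall is.**

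- *Attrition.* With no loss (101 per arm), change-score power is 85 % at r = 0.3 and 90 % at r = 0.4. With 20 % loss (80.8 per arm) it is 76 % and 82 %.
- *Unequal SDs.* The change score does worse than the 1-year score when r < s₀/(2s₁). With equal SDs that is 0.5. With an assumed baseline SD of 15 and follow-up SD of 20 it is 15/40 = 0.375. Power at 65.65 per arm is then 77 % at r = 0.3 and 83 % at r = 0.4.
- *Pattern of effect.* Take an interaction test over all five time points (compound symmetry, 65 per arm) with a 10-point difference at all four later visits. Power is 67 % at r = 0.3 and 75 % at r = 0.4. If the difference is present only at one and two years, power is 86 % and 91 %.

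**The case against.** The strongest reply is that this is one sentence in a condensed article. Covariates and model terms are commonly left to a full protocol or analysis plan, which is not shown here, and the text nowhere says that baseline will go unadjusted. An unadjusted comparison of randomised groups is valid, and it meets the stated power.

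Much of this stands. The point can only be that this text names a method without adjustment, not that no adjustment will ever be made. But the article does state a comparative method, and a more precise one is available from data it already plans to collect. That makes this an improvement to a stated choice rather than a complaint about missing detail.

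Two stronger readings are tempting, and the documents support neither.

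- *That the trial will miss its stated 80 % power.* This needs four things together: a group-by-time primary test, r below about 0.5, similar SDs at baseline and 1 year, and attrition near the full allowance. The words on within-group and longitudinal differences allow a group-by-time reading but do not specify it as the primary test. No value of r is given. The 35 % is an allowance, not a forecast.
- *That omitting diagnosis is a defect of the same kind.* The four diagnoses are pooled and not stratified, and the Discussion calls the population heterogeneous. But the article gives no ODI variance by diagnosis, so any gain cannot be quantified. Since allocation was not stratified, the design does not require the adjustment.

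**Conclusion.** The point holds as an efficiency recommendation. The analysis as worded leaves out a baseline measurement that would make the 1-year comparison more precise whenever r is not zero. At the tolerated 35 % loss, the gain over an unadjusted 1-year comparison is about 4, 6 and 10 percentage points of power at r = 0.3, 0.4 and 0.5. It rests on the planned 10-point difference, SD 20 and the assumed r. The 1 − r² factor is a large-sample approximation, which is adequate at about 65 per arm with one covariate.

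There is no bias, no internal contradiction and no sample-size error. The group-by-time shortfall (67 % at r = 0.3, 74 % at r = 0.4) is conditional on the assumptions listed above. It is a reason to rule that form out in the wording, not evidence that the trial is underpowered.

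**What to change.** In Statistical methods, name the primary analysis as the between-group difference in ODI at 1 year, estimated by ANCOVA with baseline ODI as covariate. A mixed model of the post-baseline visits with baseline ODI as covariate, reporting the 1-year contrast, would serve equally. State that baseline is not a level of the time factor. Diagnosis may be added as an optional covariate, provided it is specified before the analysis.

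The Sample size section can stay as it is; with adjustment its calculation becomes conservative. The cost is wording only: no extra patients, visits or measurements. The Trial status section describes the trial as ongoing, so the change can be fixed and dated before the outcome data are analysed.
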